**Assessments**					
Initial clinical assessments***	**X**				
Clinical assessments†		**X**	**X**	**X**	**X**
Anthropometric measurements‡		**X**	**X**	**X**	**X**
6MWT		**X**	**X**	**X**	**X**
Hand grip test		**X**	**X**	**X**	**X**
Pulmonary function test§§		**X**			
Cardiopulmonary exercise testing¶¶		**X**			**X**
Blood test****		**X**	**X**		**X***
24-hour Holter ECG monitoring††††		**X**			**X**
Self-Report Questionnaires‡‡		**X**	**X**	**X**	**X**
Self-directed physical activity follow-up: email or paper logbook§§		**X**	**X**	**X**	**X**
Data collected/implementation		**X**	**X**	**X**	**X**
Data collected/risk factors for the development of AIMSS			**X**		
Semi-structured interview					**X**
Monitoring of adverse events			**X**	**X**	**X**
Monitoring of APA-related adverse events			**X** EG	**X**	**X**

* Initial clinical assessments performed by the surgeon or APN: clinical examination, identification of barriers and facilitators to regular physical activity during the medical interview and assessment of absolute and temporary contraindications to adapted physical activity.

† Clinical assessments performed by the sports medicine physician.

‡ Anthropometric measurements: weight, height, BMI, waist circumference, four skinfolds.

§ Pulmonary function test: FEV1, PEF, VT, VC, RV, TLC, DLCO correction.

¶ Cardiopulmonary exercise testing: VO₂ peak, VO₂ max, maximal heart rate, VO₂ at ventilatory threshold -VT1-, cardiac output at VT1, heart rate at VT1, blood pressure, oxygen saturation.

** Blood test: lipid profile at V0 and V1 (V2 if abnormal value at V1), fasting insulin and fasting blood glucose at V0 (V1 if abnormal value at V0 and V2 if persistent abnormal value at V1), C-reactive protein at V0 (V1 and V2 if inflammation is suspected).

†† 24-hour Holter ECG monitoring: total spectral power.

‡‡ Self-Report Questionnaires (cf. table 2).

§§ Self-directed physical activity follow-up: type, intensity (Borg scale), duration, frequency of physical activity and adverse effects of PA.

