### Sample size

#### Sample size for the primary outcome

The expected prevalence of AIMSS in the standard care group is approximately 40%. We hypothesise a 50% reduction (20%) in the experimental group with early implementation of APA.^20^ Considering an alpha risk of 5%, a power of 80% and a two-sided hypothesis, 82 patients per arm will be required. Assuming 10% unusable data, a total of 182 patients will be included.

Sample size for the qualitative component of the mixed-methods study (secondary implementation aim).

The principle of theoretical saturation will guide the sample sizes of the two groups (patients and healthcare professionals), once the collected data are sufficient to explain the phenomenon. Data collection, conducted progressively and in parallel with analysis, will define the final sample size.^21^

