#### Secondary data collection: risk factors for the development of AIMSS

To investigate potential risk factors for the development of AIMSS, the following data will be collected: clinical, demographic, pathological and therapeutic variables; beliefs and perceptions in relation to hormone therapy will be assessed using the BMQ-AET (Beliefs about Medicines Questionnaire - Adjuvant Endocrine Therapy); and pain catastrophising will be measured using the Pain Catastrophising Scale.

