### Data analysis

#### Quantitative data analysis

The statistical analysis will be performed on the intention-to-treat population.

For the primary objective, the maximum intensity of musculoskeletal pain at 6 months (T2) will be compared between groups using parametric (eg, t-test) or non-parametric (eg, Wilcoxon-Mann-Whitney) tests, depending on data distribution.

Secondary objectives include evaluating the intervention’s effects on outcomes such as physical health, psychosocial well-being and treatment adherence. Analyses will include: (1) between-group comparisons at specific time points (T0, T1, T_APA_, T2), (2) between-group comparisons of change over time (eg, T0–T1, T1–T2) and (3) within-group longitudinal changes across time points.

Univariate and multivariate logistic regression models will explore factors associated with the occurrence of AIMSS. Qualitative variables will be compared using χ^2^ or Fisher’s exact test, as appropriate.

All analyses will be two-sided with a significance threshold of p<0.05. Missing data will be handled using appropriate statistical methods. Analyses will be conducted using R software (R Foundation for Statistical Computing, Vienna, Austria).

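### AIMSS risk-factor data are taken at T1, after APA has begun in one arm only, and the planned single-predictor logistic models carry no term for arm

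*Protocol article*

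**What the plan says.** Under Quantitative data analysis, the article plans that "Univariate and multivariate logistic regression models will explore factors associated with the occurrence of AIMSS". It does not say whether the multivariable model contains randomised arm, whether the arms are combined or analysed separately, or how many predictors are considered.

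The section on secondary data collection for risk factors lists "clinical, demographic, pathological and therapeutic variables", together with the BMQ-AET (beliefs about endocrine therapy) and the Pain Catastrophising Scale. In Table 1 the row "Data collected/risk factors for the development of AIMSS" is marked in the T1 column and nowhere else. Neither scale appears among the Table 2 questionnaires.

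The same table starts APA at T0 in the experimental arm and at T1 in the control arm. The section on assessment times puts 1 to 7 months between T0 and T1.

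The sample-size section expects about 40% AIMSS under standard care and adds: "We hypothesise a 50% reduction (20%) in the experimental group with early implementation of APA".

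**The concern.** Two things that the article fixes work against each other. The predictors are recorded when one arm has been exposed to the intervention and the other has not. The univariate models then relate those predictors to AIMSS without the variable that the trial itself expects to be a strong determinant of AIMSS.

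Suppose APA lowers catastrophising by T1 and also lowers AIMSS by some other route. Control patients will then tend to have both higher scores and more AIMSS. Across the two arms together, catastrophising will look like a risk factor even if it has no effect within either arm. What it would really mark is not having had early APA.

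The abstract names identification of AIMSS risk factors as a secondary aim, and the Discussion wants to use it to find the most vulnerable patients. A factor that stands in for allocation would mislead that use.

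**Working it through.** **Inputs from the article.** AIMSS 40% in control and 20% in experimental; "Considering an alpha risk of 5%, a power of 80% and a two-sided hypothesis"; "82 patients per arm will be required"; 10% unusable data; 182 in total.

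**The plan's own figure.** With the pooled-variance formula for two proportions (mean proportion 0.30):

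n = [1.960 × √(2 × 0.3 × 0.7) + 0.842 × √(0.4 × 0.6 + 0.2 × 0.8)]² / 0.2² = 81.2, rounded up to 82 per arm.

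Then 164/0.9 = 182.2, in line with 182. The stated size reproduces.

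**Assumed effect of arm.** OR = (0.2/0.8)/(0.4/0.6) = 0.375.

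**Expected events.**
- 164 evaluable patients: 82 × 0.40 + 82 × 0.20 = 32.8 + 16.4 = 49.2.
- All 182 patients: 91 × 0.40 + 91 × 0.20 = 54.6.
- At 10 events per parameter (a rule of thumb, not in the article): 4.9 to 5.5 parameters.

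**How the confounding arises.** Let a T1 score have no effect on AIMSS within arm, and let APA lower it by s SD.
- Share of experimental patients among those with AIMSS: 16.4/49.2 = 0.333.
- Share among those without: 65.6/114.8 = 0.571.
- Mean score is therefore higher in AIMSS cases by s × (0.571 − 0.333) = 0.238 s.
- The standard error of that difference is about √(1/49.2 + 1/114.8) = 0.170, slightly more once the shift widens the spread.

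At s = 0.5 the difference is 0.119, the standard error 0.175 and z = 0.68. The chance of two-sided p<0.05 is then about 10.4%. At s = 0.8, z = 0.190/0.182 = 1.04, which gives about 18%.

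**Simulation.** 82 per arm, 40% against 20%, 2,000 trials per setting, logistic regression on the null predictor with and without arm:

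| Assumed APA shift (SD) | p<0.05, no arm term | p<0.05, arm included | Mean spurious OR per SD, no arm term |
|---|---|---|---|
| 0 | 4.2% | 4.4% | 1.00 |
| 0.2 | 6.3% | 5.0% | 1.05 |
| 0.3 | 6.4% | 4.5% | 1.07 |
| 0.5 | 10.5% | 5.4% | 1.12 |
| 0.8 | 17.6% | 5.1% | 1.18 |

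Monte Carlo error is about 0.5 percentage points near 5% and 0.9 near 17%. Two further simulations of this kind gave 9.9% and 10.8% at 0.5 SD, and 16.8% and 17.5% at 0.8 SD. The hand calculation and the simulations agree.

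**The case against.** The strongest reply is that the article condenses a fuller plan. Covariates, adjustment terms and model-building rules are commonly left to the SAP, which is not shown. The list of risk-factor data is a collection list, not a model specification, so the absence of arm from it proves nothing about the multivariable model. That stands. A reader might infer that the risk-factor models pool the arms and leave arm out throughout, but the article is silent on both.

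A second reply is that T1 is a sensible baseline. It is the start of the aromatase inhibitor, it precedes the T2 outcome, and it is a natural time to ask about beliefs on hormone therapy. This also stands: T1 measurement is not wrong in itself. It is a problem only where arm is not accounted for.

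Third, the inflation needs APA to move the predictor, and the article gives no size for that. At 0.2 to 0.3 SD the excess is one or two percentage points. Demographic and pathological factors, and tumour treatments, are not plausibly moved by APA. An effect on beliefs about hormone therapy is less obvious than one on catastrophising. Nor is the T0 to T1 interval a measure of APA exposure, because the supervised programme lasts 12 weeks and may then be renewed or replaced. All of this limits the reach of the point.

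Fourth, a reader might infer that about 49 events are far too few for the planned model, or that variables will be screened on univariate p-values. The article gives no number of candidate parameters and states no selection rule, so neither inference is supported.

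What the replies do not remove is the commitment to univariate models. A single-predictor model has no arm term by definition, whatever the SAP says about the multivariable one.

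**Conclusion.** The point holds in a limited form. The single-predictor results for T1 variables that APA can change, chiefly the Pain Catastrophising Scale and possibly the BMQ-AET, can be confounded by arm. The false-positive rate for a null predictor goes from the nominal 5% to about 6% for a small shift, 10% for a 0.5 SD shift and 17% for a 0.8 SD shift. Including arm returns it to about 5%.

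This rests on three assumptions: the univariate models are fitted to both arms together, which the article does not state; arm has the planned effect on AIMSS; and APA shifts the predictor by the amounts shown. If any one fails, the inflation shrinks or disappears.

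The event count is a secondary caution. About 49 events, or 55 if all 182 patients contribute, leave room for about 4 to 5 parameters. That is a constraint to plan within, not a demonstrated overfit.

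The primary comparison is untouched. This is a minor improvement to an analysis that the article itself words as exploratory.

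**What to change.** - Include randomised arm in every AIMSS risk-factor model, including those that examine one factor at a time. Report each such factor as adjusted for arm.
- For any modifiable predictor that is also measured at T0, use the T0 value. On the article's schedule this cannot help the Pain Catastrophising Scale or the BMQ-AET, which are collected at T1 only; for them, the arm term does the work.
- Keep the multivariable model to about 4 to 5 pre-named parameters, of which arm takes one, or fit a larger set with a penalised logistic model.

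The cost is a few lines in the analysis plan. No extra patients, visits or data are needed. The downside is fewer candidate factors in the multivariable model, or estimates shrunk towards no effect.

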#### Qualitative data analysis

Data will be analysed using a combined deductive and inductive approach to ensure rigour, transparency and reproducibility.^22^ Transcripts will first be deductively coded using the 14 domains of the TDF and COM-B model.

Second, an inductive thematic analysis, following Braun and Clarke’s six-phase methodology,^26^ will be conducted to capture themes not represented within the TDF.

Finally, inductive and deductive codes will be integrated to develop interpretative themes and subthemes, each labelled with a clear, representative title.

## Discussion

The APIS study evaluates the effectiveness of an APA programme initiated early in the oncology care pathway, while also analysing the contextual factors that influence its implementation in routine practice. It further contributes to a better understanding of the risk factors for AIMSS, to identify the most vulnerable patients and support treatment adherence.

### Effectiveness and implementation: justification for a hybrid protocol

This study adopts a type 1 hybrid effectiveness–implementation design, an approach increasingly recommended given the complex, multilevel barriers to integrating PA into routine cancer care. This dual ambition implies the combined use of quantitative and qualitative methods, applied in a complementary manner, along with specific theoretical frameworks and models. The study’s apparent complexity is therefore intentional and justified: it enables evaluation of the clinical effectiveness of a complex intervention, while also providing valuable insight into the real-world interdisciplinary collaboration and the perceived facilitators and barriers reported by patients and healthcare professionals.^27^

### Interdisciplinary roles and the contribution of APNs

The APIS study will also explore the emerging role of APNs, positioned at the interface between clinical care and care coordination. APNs, such as clinical nurse specialists and nurse practitioners, can strengthen patients’ motivation to engage in APA by using strategies such as motivational interviewing, explaining cancer-specific benefits through personalised education and prescribing APA programmes. They can also facilitate access to appropriate resources, including community-based programmes or digital tools such as apps, thereby supporting continuity of care and behaviour change.^28^

Implementation data will highlight the complementary contributions of each professional within the interdisciplinary team, including APNs. These results will strengthen care models that support the integration of APA into patients’ daily lives, thereby promoting treatment adherence and quality of life.

### Patient-centred APA model

The APA programme proposed in the APIS study was designed to be individualised and responsive to patients’ needs, preferences and constraints. Its patient-centred design, coupled with a gradual transition toward self-directed activity, supports long-term goals of autonomy, sustainability and integration into daily life. This design aligns with current oncology recommendations advocating the personalisation of supportive care interventions and seeks to enhance adherence through a flexible, engaging framework.^29^

Importantly, patients in both the intervention and control groups are free to engage in PA independently, without restrictions. While this openness may introduce a potential bias, it is anticipated in the study protocol. A daily monitoring system, using either email or a paper logbook, has been implemented to capture all PAs performed, whether spontaneous or guided.

By accounting for these real-life conditions, the APIS study aims to provide a nuanced interpretation of its findings and strengthen the validity and applicability of the data regarding both the effectiveness of the intervention and its integration into routine care.

Moreover, a patient-researcher plays an active role in all phases of the study, contributing to its relevance, acceptability and patient-centredness and reinforcing its overall applicability.

### Limitations

Several limitations are anticipated in this study and have been carefully considered during the design phase.

First, because the intervention is behavioural, participant blinding is not feasible, which may introduce performance or reporting bias. However, this risk is partially mitigated by the inclusion of both objective clinical and paraclinical outcome measures.

Second, the use of emails or self-reported PA logs may be subject to recall or social desirability bias, even though these tools are well-validated. Their use was favoured over connected devices designed for automatic data collection. This methodological choice is based on patient feedback, which highlighted a preference for simple ones that are closer to their real-life experience.^30^

Finally, while the qualitative sample size will be guided by data saturation, transferability may be limited to similar hospital-based settings. This study represents an initial step within a type 1 hybrid design. Should the findings be positive, a subsequent phase is planned to involve community-based healthcare professionals and APA associations to support broader scaling and integration across diverse care pathways.

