## Method

### Study design

The APIS trial is a type 1 hybrid randomised controlled trial (RCT), evaluating the effectiveness of the intervention, while also collecting data on key implementation factors in real-world conditions.^16^ This study is designed as an open-label, two-arm, parallel, multicentre, RCT. Patients in the experimental group will begin a personalised APA programme at the start of primary treatment (surgery or neoadjuvant chemotherapy), in parallel with their usual treatment, as illustrated in figure 1. Patients in the control group will receive standard care, with the structured APA programme initiated at the beginning of the AI therapy, namely at the end of primary treatment. In the absence of standardised real-world data on when to initiate APA in postmenopausal women with hormone-sensitive breast cancer, the timing chosen for the control group reflects current local practice. Both groups will have no restrictions on autonomous PA during their care pathway.

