### Assignment of interventions

Participants will be randomised using Ennov Clinical software. Randomisation will be stratified. The study centre will use a computer-generated pseudo-randomised list prepared in advance by a biostatistician. Given the behavioural nature of the intervention, blinding will not be possible.

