### Intervention

The APA programme, delivered by the sports medicine department, will consist of structured exercises supervised by APA professionals and will be identical for all patients enrolled. The only difference between the two groups is the timing of the intervention within the care pathway: either initiated at the diagnosis of cancer or at the introduction of AI. The APA programme will begin, after a medical evaluation, with a 12-week supervised programme. Each week, the patient will have two 1 hour sessions supervised by a physiotherapist and/or an APA instructor. At the end of the initial 12-week APA programme, the sports medicine physician assesses the patient’s progress and goal attainment to decide whether to renew the programme, refer the patient to a supervised community-based PA, or guide her toward self-directed activity.

After 12 weeks, a new medical consultation will be scheduled, and a new renewal or adjustment phase will begin until the end of the trial.

The detailed APA programme is provided in online supplemental file 1.

In addition to this personalised programme, the interdisciplinary care team will encourage patients to remain physically active throughout the rest of the week, according to their individual abilities. The goal will be for patients to develop specific skills that will support long-term lifestyle changes.

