### Outcomes

#### Primary outcome

The primary outcome will be the score for the most intense musculoskeletal pain, assessed with the Nordic-style questionnaire, 6 months after the introduction of the AI (T2).

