### Data collection

All functional tests and measurements will be performed as part of routine care in a sports medicine department by professionals trained to ensure the reliability, reproducibility and standardisation of the assessments.

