#### Primary data collection

The prevalence of musculoskeletal pain will be assessed using the Nordic-style questionnaire, a validated tool for detecting musculoskeletal disorders. It consists of closed-ended questions and can be used as a self-reported questionnaire.

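### Blinding is ruled out for everyone on a reason that covers only participants and exercise staff, and the objective measures offered as partial mitigation do not protect the self-reported primary pain score

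*Protocol article*

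**What the plan says.** Under Study design the protocol states: "This study is designed as an open-label, two-arm, parallel, multicentre, RCT". Assignment of interventions then says: "Given the behavioural nature of the intervention, blinding will not be possible". That sentence does not separate participants, APA staff, testers and analysts.

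The Limitations section is narrower. It says that "because the intervention is behavioural, participant blinding is not feasible, which may introduce performance or reporting bias", and adds that "this risk is partially mitigated by the inclusion of both objective clinical and paraclinical outcome measures".

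On the outcome that decides the trial, the Primary outcome section says: "The primary outcome will be the score for the most intense musculoskeletal pain, assessed with the Nordic-style questionnaire", measured at T2. Primary data collection describes the instrument: "It consists of closed-ended questions and can be used as a self-reported questionnaire". Table 2 also marks it as a self-report questionnaire.

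On who delivers and who measures, the Intervention section says: "The APA programme, delivered by the sports medicine department, will consist of structured exercises supervised by APA professionals". Data collection says that functional tests and measurements are "performed as part of routine care in a sports medicine department", by professionals trained in standardised assessment. No masked or independent tester is described.

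**The concern.** Two statements reach further than their support.

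- **The exclusion of blinding.** A woman knows when she started exercising, and so do her trainers. That does not explain why the statistician must know the arm codes, or why every tester must know the arm. The Limitations section argues the case for participants only.
- **The mitigation.** It is offered against performance or reporting bias. The outcome most exposed to reporting bias is the primary one, a pain score that the woman gives herself while knowing her arm. An objective measure of something else cannot correct that score.

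At stake is how a positive result would be read. If women assigned to early APA report less pain partly because they expect less, the primary comparison takes in that difference, while the protocol points to a safeguard that does not act on it. Some of the functional tests also depend on effort and encouragement, so they are not a clean external check.

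**Working it through.** **1. Who the stated reason covers**

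| Role | Does a behavioural intervention rule out masking? | Reason given in the protocol |
|---|---|---|
| Participant | Yes | Assignment of interventions; Limitations |
| APA staff | Yes, by nature of the task | Assignment of interventions (general statement) |
| T2 functional tester | Not by itself | None specific |
| Analyst | No | None |

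**2. What the mitigation reaches**

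| Outcome | Status | Exposure to expectation or tester influence |
|---|---|---|
| Nordic-style worst-pain score, T2 | Primary | Self-reported; exposed |
| Other questionnaires in Table 2 | Secondary | Self-reported; exposed |
| 6-minute walk, grip, maximal-effort exercise values | Secondary | Effort and encouragement; exposed |
| Exercise-test values at the first ventilatory threshold | Secondary | Submaximal; much less exposed |
| Blood tests, 24-hour Holter | Secondary | Much less exposed |

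No measure in the last two rows measures pain.

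**3. Where delivery and testing meet.** The Intervention section places delivery in the sports medicine department and has the sports medicine physician review progress and decide on programme renewal. The T1 visit is held in that department with that physician, T2 follows the T1 procedure, and a footnote to Table 1 assigns the clinical assessments to the same role. Delivery and assessment are therefore not described as separate.

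**4. Why analyst masking has a purpose.** Quantitative data analysis leaves the primary test, parametric or rank-based, to the distribution of the data, and leaves missing data to unspecified methods. If these choices are still open when data arrive, they are better made without knowledge of arm.

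**5. Scale of a reporting shift (illustration).** First, the plan's own figure. Inputs from Sample size: 40% against 20%, two-sided alpha 5%, power 80%. With pooled variance and no continuity correction:

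n = [1.96·√(2 × 0.30 × 0.70) + 0.842·√(0.24 + 0.16)]² / 0.20² = (1.270 + 0.532)² / 0.04 ≈ 81.2, so 82 per arm, as stated.

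Now assume no true effect, 82 analysed per arm, and a shift in reporting in the early-APA arm only. The sizes of shift are assumptions and do not come from the documents.

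- On the prevalence scale, for p₁ = 0.40 and reported p₂: P(false benefit) = Φ{[(p₁ − p₂)·√82 − 1.96·√(2p̄(1 − p̄))] / √(p₁(1 − p₁) + p₂(1 − p₂))}. For p₂ = 0.35: (0.4528 − 1.3419) / 0.6837 = −1.300, which gives 9.7%.
- On the score scale, for a shift of d standard deviations: Φ(d·√(82/2) − 1.96). For d = 0.2: 1.281 − 1.960 = −0.679, which gives about 25%.

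| Assumed shift | Probability of a false benefit |
|---|---|
| None | 2.5% |
| 2 points | 4.5% |
| 5 points | 9.7% |
| 10 points | 26.7% |
| 0.1 SD | about 9% |
| 0.2 SD | about 25% |
| 0.3 SD | about 48% |

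Adding objective secondary outcomes changes none of these probabilities, and neither would masking the functional testers.

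**The case against.** The case on the other side has real weight.

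- **The limitation is disclosed.** The trial is called open-label, the bias is named, and only partial mitigation is claimed. A reader might infer that the protocol presents the objective measures as protecting the pain outcome. It does not say so. What stands is that it does not say which outcomes the mitigation covers, and the primary is not among them.
- **Tester masking does not touch the primary outcome.** This is correct. It would protect secondary functional tests only.
- **Loyalty to the delivering team is not clearly differential.** By T2 both arms have started the same programme in the same department. A reader might infer that loyalty favours early APA, but the documents do not support that. Differential expectation about early timing remains possible.
- **Masking at T2 is not shown to be feasible.** A reader might infer that, because both arms have started the programme by T2, testers would have no cue to the arm. But the sports medicine physician both assesses and decides on renewal, and the end-of-programme visit falls at different points of the pathway in the two arms, so records can reveal the arm. The document gives no staffing figures.
- **Not every objective measure is weak.** Blood tests, Holter and submaximal exercise values are fairly called objective, and testers are said to be trained for standardisation.
- **Tester rosters and masked codes are often left to the full protocol or the SAP.** This is true, and their absence alone would be no finding. Here, however, the article states that blinding is not possible, and that statement is too broad.

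**Conclusion.** The point holds in a limited form. The exclusion of all blinding is wider than its reason, which covers participants and APA staff. The objective measures are all secondary and give no protection to the self-reported primary score. Three kinds of functional result (6-minute walk, grip and maximal-effort exercise values) are themselves open to tester influence.

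The documents do not allow the bias to be sized. The false-benefit probabilities show only how sensitive 82 per arm would be to an assumed reporting shift. They rest on no true effect, a shift in one arm only, and a normal approximation. They do not predict what will happen in this trial. The sample size is unaffected.

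The documents do not support a conclusion that the trial is unsound, that masked testers would rescue the primary outcome, or that masking at T2 would certainly succeed. The reporting bias in the primary outcome can be reduced a little at the point of data entry, but the woman's own expectation remains.

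**What to change.** 1. **Assignment of interventions:** limit the statement to participants and APA staff.
2. **Analyst:** work on masked arm codes until the choice of primary test and the handling of missing data are fixed.
3. **T2 pain questionnaire:** have each woman enter it herself in Ennov Clinical before contact with the APA team at that visit. Quantitative data management already permits direct patient entry; only the timing is new. This limits staff influence, not her expectation.
4. **T2 functional tests:** where existing rosters allow, use staff who did not supervise that woman and are not told her arm, and accept that the masking may be broken.
5. **Limitations:** state that the objective measures are secondary, that they do not protect the primary outcome, and that its reporting bias remains.

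The cost is protocol wording, a dataset with masked codes and some scheduling constraint at T2. No new tests are needed and, because item 4 is conditional on existing rosters, no new staff.
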